### Main study parameter/endpoint

Pathological response rate (percentage necrosis in comparison to tumour cells in the resected specimen) after CRT, determined by an expert pathologist according to the Mandard Tumour Regression Grade (TRG).

### Secondary study parameters/endpoints

cfDNA methylation profiling and molecular characteristics of the tumour tissue.

The blood sample obtained one week after initiation of the neo-adjuvant treatment will be utilized to investigate whether the dynamics in circulating tumour DNA (ctDNA) can be employed to early assess response to this therapy, and whether this provides additional value beyond conducting only a baseline measurement. The blood samples obtained prior to surgery and two weeks post-surgery may be utilized in the future to correlate ctDNA with the secondary endpoints of recurrence-free survival and overall survival. This aspect has been explicitly discussed with our patient advocates, who expressed no concerns. In a broader context, translational research on the potential applications of liquid biopsies benefits from longitudinal sample collection, enabling the examination of the effects of various treatment modalities on the quantity of ctDNA and its ultimate clinical relevance.

Clinical features and molecular characteristics of patients with a clinical complete reponse. The analyses of this tissue will be as described above for the other tissue but this group will be investigated separately.

### Other study parameters

Patient characteristics: age, sex, length, weight, cTNM, WHO performance status, extramural vascular invasion, mesorectal fascia involvement, lateral lymph node involvement.

### Recruitment and consent participants

Patients will be asked to participate in this study by their treating physician. If the patient is interested in participation, information concerning the research purpose will be explained. They also receive information in writing (informed consent form). Patients are allowed to sign the informed consent form immediately after careful reading, if a patient needs to consider their informed consent, this will be allowed as well until the start of CRT. Prior to any study related intervention (i.e. blood sample collection when blood sampling is already clinically indicated) the informed consent form must be signed by the patient and the person who has conducted the informed consent procedure.

### Randomisation, blinding and treatment allocation

Not applicable, as no randomisation or blinding is performed.

### Study procedures

Patients with locally advanced rectal cancer scheduled to receive pre-operative chemo-radiation therapy (CRT) in the Erasmus MC will be informed about the study by the local investigator or local study coordinator. From 75 consenting patients, blood (2 × 10 ml) will be collected in cell-stabilizing blood collection tubes at 4 time points: [1] After diagnosis and before start with CRT, [2] between 1 and 2 weeks after treatment, [3] 0–3 days before surgery, and [4] between 2 and 5 weeks after surgery at the outpatient clinic visit. Blood will be collected at time points 3 and 4 for translational research. Of note, most patients (including the involved patient representatives) do not consider additional blood draws as a burden. We will ensure blood draws for the current project will coincide with hospital visits as much as possible. Next to the blood sampling we will also retrieve the formalin-fixed paraffin-embedded (FFPE) tissue biopsy obtained at diagnosis from the pathology archive for participating patients to allow comparative analyses between blood and tumour tissue. Clinical (TNM stage, tumour location, age, gender), pathological (differentiation grade, MSI status, TRG), and follow up (RFS and OS) data will be collected for all participating patients from the electronic patient files. Information about pathology material will be stored in databases from IKNL, CBS and PALGA and can be used for further information in the future. Obtained molecular results will not be communicated with the participating patients on an individual basis as this may cause unnecessary anxiety, but overall study results will be shared.

Blood will be processed into plasma within 96 h and stored at -80 degrees, according to our standard pipeline. cfDNA will be isolated from of the stored plasma, quantified, and quality will be evaluated using standard laboratory techniques.

Similarly, we will isolate RNA and DNA from diagnostic FFPE-tissue sections and evaluate the quantity and quality.

MeD-seq analysis will be done on 10 ng cfDNA from the pre-treatment sample (baseline) and after 1 week of treatment as well as on genomic DNA from the tissue specimens as described before [6, 7]. In short, DNA will be digested with LpnPI yielding 32 bp fragments around the fully methylated recognition site containing a CpG. Samples will be prepped and purified for sequencing. Multiplexed libraries will be sequenced for ~ 20 M single reads. Tissue-based MeD-seq profiles will be used to determine the most informative regions for radio-sensitivity.

RNAseq analysis will be performed on RNA isolated from the FFPE tissue specimens, which has already been successfully performed in other, technically comparable, sample cohorts (unpublished data). RNAseq data will be used to determine genes associated with radio-sensitivity and, in addition, baseline molecular characteristics of the tumour, such as hypoxia, proliferation state of the tumour [8], and the consensus molecular subtype (CMS) [9] can be inferred from this data.

For RNAseq data, raw sequencing data will be mapped to the reference genome (GRCh38) using the STAR aligner after which the duplicate reads are marked using Sambamba. Next, FeatureCounts will be used to obtain read counts for each gene. These read counts will be normalized using GeTMM to obtain the gene expression levels that can be used for downstream analyses, such as hypoxia and proliferation scores [8], as well as consensus molecular sutype (CMS) calling [9].

For MeD-seq data, processing is carried out using specifically created scripts in Python, which include a trimming step to remove the Illumina adapters and a filtering step based on LpnPI restriction site occurrence between 13 and 17 bp from the 5’- or 3’ end of the read. Reads passing the filter are mapped to the genome using Bowtie 2. Using all unambiguously mapped reads count scores will be assigned to each individual LpnPI site in the genome. From genome-wide individual LpnPI site scores count scores are generated for 2 kilobase regions surrounding all known transcription start sites using a sliding window approach. To normalize potential differences in sequencing yields, regional read counts are divided by the total read count per sample. To generate a summary cfDNA methylation score, Z scores relative to healthy control samples (data already available from data of anonymous patients who donated blood at Sanquin and gave informed consent) will be calculated for every TSS region, which we will square and sum into a genome-wide Z score.

cfDNA methylation profiles and the summary score will be compared between patients with and without pathological response to CRT and, additionally, we will investigate associations between the cfDNA methylation profile/summary score, clinical, and molecular characteristics of the tumour.

### Statistical analysis

All main analyses will be performed according to the intention to treat principle using appropriate statistical software, such as R Project for Statistical Computing version 4.0.4. (https://www.r-project.org/) and SPSS version 21.0 (SPSS inc., Chicago, IL). ctDNA methylation levels will be scored high/low relative to the median value in the cohort. Missing samples will not be replaced, because a dropout rate taken into account in the sample size calculation.

We will perform adaptive group-regularized logistic ridge regression followed by post hoc group-weighted elastic net feature selection as described before [10]. In this innovative method group-regularisation of all markers is based on auxiliary data that is provided separately to the model resulting in improved marker selection. In our case this auxiliary data will consist of tissue-based comparison measures like fold changes in DNA methylation and RNA expression between patients with and without a pathological response. When sufficiently promising a targeted assay can be developed for the most optimal marker panel to reduce costs and facilitate clinical implementation.

Obtained data from patients following a watch and wait approach due to a sustained clinical response will be analysed as a separate subgroup since in these patients no pathological response can be determined. These patients will also follow the regular follow-up and will be analysed conform the other patients, only as a subgroup.

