### Sample size calculation

To detect a 2.5 fold difference in the chance of responding to CRT between circulating tumour DNA methylation high and - low patients with an alpha of 0.05 and a beta of 0.8, we need to include at least 64 patients according to the Chi-squared statistic with the continuity correction applied to compare proportions with a dichotomous outcome between two samples (http://www.sample-size.net/sample-size-proportions/). Based on previous and on-going studies we expect ~ 15% dropout due to either technical failure or loss to follow up. Therefore we will aim to include 75 patients in this project.

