### Secondary study parameter(s)

In an exploratory analysis we will investigate whether the obtained methylation profiles are associated with our secondary outcome measures Recurrence Free Survival (RFS) and Overall Survival (OS). For this purpose we will perform univariate Cox regression analyses with the resulting methylation summary score for the entire profile as well as the selected marker panel (both continuous and dichotomized on the median). In case of significance (p < 0.1) for the univariate analysis subsequently a multivariate model will be built using known risk factors, including clinical (TNM stage, tumour location, age, gender), and pathological (differentiation grade, microsatellite instability status, TRG) parameters.

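### The only powered comparison splits the continuous methylation score at the cohort median; it meets its own 80% target but gives up power that a continuous analysis would keep

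*Protocol article*

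**What the plan says.** All references are to the protocol article.

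- **Study procedures** builds the summary score. Z scores against healthy controls are calculated for each transcription-start-site region, then squared and summed over the genome. The result is a continuous quantity.
- **Statistical analysis** then states, without limiting it to any one analysis: "ctDNA methylation levels will be scored high/low relative to the median value in the cohort".
- **Sample size calculation** sizes the study on that grouping: "To detect a 2.5 fold difference in the chance of responding to CRT between circulating tumour DNA methylation high and - low patients". The error rates are stated as "with an alpha of 0.05 and a beta of 0.8". The method is the "Chi-squared statistic with the continuity correction applied to compare proportions with a dichotomous outcome between two samples", and the result is that "we need to include at least 64 patients". No response rate is given for either group. The section does not mention the median; the link comes from reading it together with Statistical analysis.
- **Primary study parameter(s)** says that profiles and the summary score are to be compared between responders and non-responders. It names neither a test nor a cut. It then describes a separate penalised logistic model that selects a marker panel, with external validation foreseen.
- **Secondary study parameter(s)** is explicit for survival. The Cox models use the summary score for the whole profile "as well as the selected marker panel (both continuous and dichotomized on the median").

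**The concern.** Cutting a continuous predictor at its median treats a patient just above the cut like the patient with the highest score, and discards all ordering within each half. With 64 evaluable patients that information matters. The continuity correction makes the test more conservative still.

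The protocol plans the score in continuous form for the exploratory survival outcomes. For pathological response, the endpoint that the study is sized on, the only form that is spelled out is high/low.

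The cut is also relative. Half the cohort is high by construction, whatever the cohort looks like. The stated long-term purpose is to select future patients for CRT, which would need a cut-off that means the same thing outside this cohort.

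**Working it through.** **1. Reproduce the 64.** Inputs from the Sample size calculation: a 2.5-fold ratio, alpha 0.05 (taken as two-sided), the stated 0.8 read as power, and the continuity correction. Equal groups follow from the median split. The base rate p1 is not stated, so it was scanned with p2 = 2.5 × p1.

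Uncorrected size per group, with p̄ = (p1 + p2)/2:

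n = [1.960·√(2p̄(1−p̄)) + 0.842·√(p1(1−p1) + p2(1−p2))]² / (p2−p1)²

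Continuity-corrected size per group: n_c = (n/4)·[1 + √(1 + 4/(n·|p2−p1|))]²

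At p1 = 0.25, p2 = 0.625 and p̄ = 0.4375: n = (1.375 + 0.547)²/0.375² = 26.26. Then n_c = 31.37, rounded up to 32 per group, **64 in total**.

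| Assumed rates | Total N |
|---|---|
| 20% v 50% | 90 |
| 24% v 60% | 68 |
| 25% v 62.5% | 64 |
| 26% v 65% | 60 |
| 30% v 75% | 46 |

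The plan's figure therefore fits 25% v 62.5%. That pair is back-calculated, not stated. Reading 2.5 as an odds ratio would need 170 to 210 patients for base rates of 20% to 50%, so a ratio of proportions is meant.

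**2. Compare the split with the continuous score.** Simulation: a standard-normal score and a logistic relation with response, calibrated so that the two halves respond at 25% and 62.5% (odds ratio about 3.06 per SD). All tests are two-sided at 5%.

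| Setting | Continuous | Split, corrected | Split, uncorrected |
|---|---|---|---|
| n = 64 | 97% | 82% | 88% |
| n = 36 | 81% | 52% | 66% |
| n = 54 | about 95% | about 71% | 78% |
| n = 64, 70% of the effect | about 81% | about 56% | 64% |

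Repeat runs of the last two rows gave 94% to 95% v 70% to 71%, and 81% v 54% to 56%.

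At n = 64 the gap is 97 − 82 = 15 points. About 97 − 88 = 9 come from the split and about 88 − 82 = 6 from the correction. For small effects and a normal score, a median split keeps 2/π = 64% of the information.

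The 54 is 64 × 0.85 = 54.4. It assumes that a further 15% have no pathological response because they follow watch and wait. The protocol says that response cannot be determined in such patients, but its allowance reads "we expect ~ 15% dropout due to either technical failure or loss to follow up" and does not name them. The 15% is an assumption.

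**3. Vary the assumptions, n = 64.**
- Rates in the lower-response half from 20% to 28%, ratio 2.5: continuous 89% to 99%, corrected split 62% to 91%.
- Strongly skewed (lognormal) score entered untransformed: continuous 90%; ranks of the same score 97%.
- Response that truly steps at the median: continuous 69%, ranks 75%, split 73% corrected and 81% uncorrected. There is no clear gain here.

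**4. Precision of the cut.** The population percentile at which the median of 64 patients falls is approximately Beta(32.5, 32.5). Its 95% range runs from the 38th to the 62nd percentile.

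**The case against.** Four points count on the other side.

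- **The plan meets its own target.** At 64 patients the corrected split has about 80% power for the effect that reproduces the sample size. This stands: the loss is relative to a better analysis, not to the plan's promise.
- **The main comparison may not be dichotomised at all.** Primary study parameter(s) names no cut, and a continuous comparison would fit its wording. A reader might infer that the continuous score is discarded for response; the document does not say so. It is ambiguous. But the high/low rule is stated without restriction, and the sample size rests on it, so the ambiguity should be settled in the text.
- **The cut is not the intended prediction rule.** A reader might infer that the threshold could never be applied to a new patient, or that the study yields nothing that can be validated. Neither is supported. The score is standardised to healthy controls outside the cohort, so the observed median could be fixed as a number and used later. The penalised marker panel is the intended predictor, and external validation is foreseen for it. What remains is narrower: the high/low cut is data-dependent, imprecise, and not itself scheduled for validation.
- **The gain is conditional, and the study is exploratory.** The response rates, the shape of the score and the smooth effect are all assumed, and under a step at the median the advantage disappears. The study also has no clinical consequences for its participants. This limits the weight of the point, but the change costs almost nothing.

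**Conclusion.** The point holds as one of avoidable inefficiency and of an unsettled main test. If response changes smoothly with a roughly normal (or suitably transformed) score, and the rates are near 25% v 62.5%, the continuous analysis has about 97% power at 64 patients against 82% for the planned corrected split. It would reach about 81% with 36. The advantage is larger where the study is most exposed: about 95% v 71% if only 54 patients have a pathological response, and about 81% v 56% at 70% of the effect. Across rates of 20% to 28% in the lower-response half, the ranges are 89% to 99% and 62% to 91%. These figures rest on assumptions that the protocol does not supply, and there is no clear gain under a step at the median. The study is not underpowered by its own terms on this account, and its route to a validated predictor, the marker panel, does not depend on the cut.

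**What to change.** In Statistical analysis and Primary study parameter(s):

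1. State that the single main test of the summary score against pathological response, at the 5% level, is a logistic regression on the continuous score, log-transformed and standardised. Report the likelihood-ratio test, the odds ratio per SD, and the AUC with a confidence interval.
2. Check linearity, for example with a spline.
3. Keep the median split for description only.
4. State the response rates behind the 64 in the Sample size calculation.
5. If a cut-off is to be carried forward, freeze it as a number on the score's scale before external validation.

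The cost is a few sentences, with no extra patients, samples or assays. The small downside is that the test assumes an approximately monotone relation on the transformed scale, which the linearity check addresses in part.

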### Primary study parameter(s)

cfDNA methylation profiles and the summary score will be compared between patients with and without pathological response to CRT and, additionally, we will investigate associations between the cfDNA methylation profile/summary score, clinical, and molecular characteristics of the tumour. To obtain the most optimal panel of methylation markers predicting pathological response to CRT, we will perform adaptive group-regularized logistic ridge regression followed by post hoc group-weighted elastic net feature selection as described before [18]. In this innovative method group-regularisation of all markers is based on auxiliary data that is provided separately to the model resulting in improved marker selection. In our case this auxiliary data will consist of tissue-based comparison measures like fold changes in DNA methylation and RNA expression between patients with and without a pathological response. When sufficiently promising a targeted assay can be developed for the most optimal marker panel to reduce costs and facilitate future clinical implementation pending external validation of our findings. When available for the selected markers we will use publicly available data for this purpose and otherwise we will contact our network to find/collect a suitable sample cohort.

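### Watch-and-wait patients count towards the 75 but leave the primary comparison because of their response, which the sample size does not allow for and the intention-to-treat label contradicts

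*Protocol article*

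**What the plan says.** - **Outcome.** Main study parameter/endpoint defines pathological response by Mandard TRG, read in the resected specimen.
- **Primary comparison.** Under Primary study parameter(s), "cfDNA methylation profiles and the summary score will be compared between patients with and without pathological response to CRT". The penalised regression classifier uses the same two classes, as do the tissue fold changes that guide its marker selection.
- **Watch and wait.** Under Statistical analysis, patients followed without surgery after a sustained clinical response "will be analysed as a separate subgroup since in these patients no pathological response can be determined". Objectives and Secondary study parameters/endpoints also treat them as a group of their own.
- **Eligibility.** The inclusion and exclusion criteria turn on the planned neoadjuvant treatment. They do not exclude patients who later avoid surgery, so these patients count towards the 75.
- **Analysis principle.** The section that sets the watch-and-wait group apart also says: "All main analyses will be performed according to the intention to treat principle".
- **Sample size.** "we need to include at least 64 patients", and for the margin above that, "we expect ~ 15% dropout due to either technical failure or loss to follow up". The target is 75.

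**The concern.** Whether a patient enters the primary comparison depends on what happened after treatment. Those who leave are patients who appeared clinically to respond well. The predictor is measured before chemoradiation, when nobody knows who will later go to watch and wait, and the stated purpose is to identify non-responders upfront. The population in which the marker would be used therefore includes patients absent from the analysis that builds and tests it.

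Three things are at stake: the number of patients in the powered comparison; the observed response rate, and with it the predicted probabilities; and possibly the strength of the association itself. The label on the analysis set also does not describe what will be done.

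**Working it through.** **1. Reproduce 64 and 75.** Sample size calculation gives the effect ("To detect a 2.5 fold difference in the chance of responding to CRT between circulating tumour DNA methylation high and - low patients"), the error rates ("with an alpha of 0.05 and a beta of 0.8", read as power 0.80) and the test ("according to the Chi-squared statistic with the continuity correction applied to compare proportions with a dichotomous outcome between two samples"). A two-sided test is assumed. The median split gives equal groups. The base rate is not stated, so it is found by scanning the lower rate at a ratio of 2.5: 24% gives 68 patients, 25% gives 64, 26% gives 60.

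With p1 = 0.25, p2 = 0.625, mean 0.4375, difference 0.375:

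- Uncorrected n per group = [1.96·√(2·0.4375·0.5625) + 0.8416·√(0.25·0.75 + 0.625·0.375)]² / 0.375² = 26.26
- Corrected n = (26.26/4)·[1 + √(1 + 4/(26.26·0.375))]² = 31.4, so 32 per group and **64 in total**
- Odds ratio = (0.625/0.375)/(0.25/0.75) = 5.0
- Power at 32 per group is 0.81 by normal approximation and 0.83 by exact binomial calculation.

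64/0.85 = 75.3, which agrees with 75. In reverse, 75 × 0.85 = 63.75, so the stated dropout uses the whole margin.

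**2. Numbers left.** The watch-and-wait share w among otherwise evaluable patients is not documented; 5 to 20% is assumed. Remaining = 63.75·(1 − w). Enrolment needed to keep 64 = 64/[0.85·(1 − w)].

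| w | Remaining | Enrolment for 64 |
|---|---|---|
| 5% | 61 | 80 |
| 10% | 57 | 84 |
| 15% | 54 | 89 |
| 20% | 51 | 95 |

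**3. Scenario A: watch and wait unrelated to methylation among responders.** Groups are fixed at the median of the full evaluable cohort. The protocol's hypothesis makes the low-methylation half the favourable one. Of 64 patients, 28 respond: 20 with low and 8 with high methylation.

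At w = 10%, 6.4 patients leave, a fraction 6.4/28 = 0.229 of responders. The low group keeps 15.4 responders and 12 non-responders (56.2%). The high group keeps 6.2 and 24 (20.5%). Odds ratio = (15.4/12)/(6.2/24) = 5.0, unchanged. The ratio of proportions rises to 2.75.

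**4. Scenario B: all the deepest responders leave.** A latent depth of response is calibrated to 25% v 62.5%, and the top w of it is removed without exception.

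| w | A: power (odds ratio 5.0) | B: power | B: odds ratio |
|---|---|---|---|
| 5% | 0.77 | 0.69 | 4.4 |
| 10% | 0.73 | 0.57 | 4.0 |
| 15% | 0.67 | 0.49 | 3.6 |
| 20% | 0.60 to 0.65 | 0.37 | 3.4 |

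The range at 20% in A is the normal approximation against the exact calculation with group sizes rounded to whole patients. For B, a second form of the latent model, normal within each half, gives power 0.70/0.58/0.52/0.38 and odds ratios 4.45/4.04/3.70/3.41.

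**5. Observed response rate.** If the patients who leave would have been responders, the rate becomes (0.4375 − w)/(1 − w): 41, 38, 34 and 30%, against 44% in the full cohort. This is the same in A and B.

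**The case against.** The handling is disclosed and reasoned. An unresected patient cannot have a TRG, and the watch-and-wait group has its own objective and analysis. The study calls itself exploratory, has no consequences for its patients, and makes implementation depend on external validation. Intention to treat has no arm-preserving meaning without randomisation, so that conflict is one of labelling. All of this stands and lowers the severity. It does not supply the missing allowance in the sample size or an analysis that includes these patients.

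A reader might infer more than the documents support:

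- *That the association is necessarily attenuated.* Scenario A shows no change in the odds ratio. Attenuation needs responders who go to watch and wait to have more favourable methylation than responders who are resected. The Discussion's link between high methylation and resistance makes this plausible, no more. Scenario B is an extreme. With imperfect selection on depth, the odds ratio at 15% is about 4.2. On the plan's own scale, the ratio of proportions, even scenario B moves only from 2.50 to about 2.33 at 15%.
- *That the classifier sees only partial responders.* Resected patients with complete regression stay in. A clinical complete response is also not proof of a pathological one.
- *That patients with regrowth re-enter with a late TRG.* The article does not say how regrowth is handled.
- *That the pathological primary endpoint must be replaced by a composite.* That would change the question asked, and the choice is debatable.

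**Conclusion.** The concern holds in a limited form. Watch-and-wait patients are enrolled, are not covered by the 15%, and leave the primary comparison because of their post-treatment response. If the planned dropout occurs, any share above zero takes the comparison below 64. In both scenarios examined, power falls below the planned 0.80, to between about 0.77 (5%, unrelated to methylation) and 0.37 (20%, all the deepest responders leave), and the observed response rate is too low for the enrolled population. The association may be attenuated; that is conditional.

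The sizes rest on a back-solved base rate of 25%, a two-sided test, the printed beta read as power, an assumed share of 5 to 20%, and watch-and-wait patients being true responders. The intention-to-treat statement conflicts with the plan whatever the share.

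**What to change.** 1. **Sample size calculation:** restate the expected evaluable number and power for the primary comparison, with an explicit watch-and-wait allowance and the assumed response rates.
2. **Statistical analysis:** replace the intention-to-treat statement by the actual analysis set, namely patients with an evaluable baseline cfDNA sample and a TRG.
3. **Statistical analysis and Primary study parameter(s):** add a prespecified analysis of the median-split comparison and the classifier in all patients with an evaluable baseline sample. Count a sustained clinical complete response at one fixed follow-up landmark, stated in advance, as response. Report it beside the TRG-only analysis, and limit conclusions from the latter to resected patients.

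The cost is wording, the choice of a landmark and one further analysis, using follow-up already collected. Enrolment rises only if the investigators want to keep 64 in the TRG comparison. The composite mixes clinical and pathological response and may misclassify a few patients; the TRG-only result beside it shows how much that matters.
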